## Abstract

Background High blood pressure (BP) affects more than one in four adults in England and only one in three patients are being treated effectively. Treatment of high BP includes changes to lifestyle such as more physical activity and/or taking medication. However, low adoption and high attrition are common with the large amounts of exercise currently recommended (>150 minutes moderate exercise per week plus 2 strength sessions). Evidence suggests that isometric exercise (IE), holding a fixed body position for a period of time, for example a wall squat, results in greater long term BP reductions, with less time and effort, than other recommended exercise. This ISOFITTER study aims to evaluate the effectiveness of IE to help reduce BP in hypertension in a real world setting. Methods A multi-centre, randomised, controlled trial of an isometric exercise wall squat intervention for hypertension employing an effectiveness-implementation hybrid type-1 design. Adults (n = 542) with Stage 1 or Stage 2 hypertension, on no more than one antihypertensive, and no other medical contra-indications will be randomised to either a standard care plus IE intervention group or standard care control group. Blood pressure readings, fidelity measurements, medications, adverse events, quality of life, participant satisfaction and health service use will be collected at baseline, week 4, month 3 and month 6 with a subgroup (n = 50) of the IE arm invited to continue for 12 months. Qualitative participant focus groups and interviews with wider stakeholders will collect implementation data. Results The ISOFITTER study will establish effectiveness of a self-administered, home-based IE intervention in lowering blood pressure in people with uncomplicated stage 1 and 2 hypertension. Implementation evidence will support patient delivery, context for scaling up of the intervention and intervention cost. Conclusion Lifestyle changes for the treatment of hypertension in the absence of other risk factors should not be overlooked. For long term hypertension management, easily adopted, evidenced exercise interventions are needed. This study will help to address this evidence gap.

## Introduction

High blood pressure (BP) or hypertension in the UK is defined as a clinic BP of ≥140/90 mmHg or a home BP measurement ≥135/85 mmHg and it is a leading modifiable risk factor for morbidity and mortality.
^1^
^,^
^2^ Hypertension may be diagnosed based on a clinic BP >140/90 confirmed by out-of-office >135/85 using either averaged home readings or ambulatory blood pressure monitoring (ABPM). BP above optimal levels (>120/80 mmHg) are linearly associated with an increased risk of cardiovascular disease (CVD) and is responsible for approximately 75,000 deaths in the UK.
^3^
^,^
^4^ It has been estimated that over ten years, 45,000 quality adjusted life years and £850 m could be saved if England and Wales achieved a 5 mmHg reduction in population systolic BP.
^5^

An estimated 32% of adults in England have high BP with three in ten of those (4.2 million) undiagnosed.
^6^ Alarmingly, data indicate that a much higher proportion of younger adults (16 to 24) with the condition remain undiagnosed compared to those aged 75+.
^7^ Adults from black minority ethnic groups are more likely to be diagnosed with hypertension.
^8^ Hypertension prevalence varies with deprivation, from 23% to 40% in the most deprived.
^9^ The United Kingdom’s (UK) Chief Medical Officer’s report (2021) emphasised increased prevalence of hypertension and cardiovascular mortality in coastal and deprived regions.
^10^ It is a top priority of the Core20PLUS5 National Health Service (NHS) strategy for reducing health inequalities across England.
^11^

National UK guidance for the treatment of hypertension is two-tiered: initial lifestyle advice (diet, weight management, exercise, reduction in alcohol and salt intake) and then anti-hypertensive medication if BP remains elevated (if clinic BP is >180/120 mmHg at first encounter or is subsequently found to be ≥150/95 on home or ambulatory BP monitoring antihypertensive medication is recommended alongside lifestyle change).
^12^ Only 40–50% of treated hypertensives achieve target BP mainly due to poor adherence, lack of efficacy of anti-hypertensives or lack of tolerability. Therefore, there is urgent need for treatments to replace or complement anti-hypertensives without compounding undesirable side effects of pharmacotherapy, often deemed unacceptable, especially to younger age groups.
^13^

The importance of lifestyle changes in hypertension treatment in the absence of other risk factors should not be overlooked.
^1^ Exercise is associated with anti-hypertensive benefits and can be as effective as medication in controlling BP.
^14^
^–^
^17^ However, low adoption and high attrition rates are common.
^14–18^ To promote lifestyle exercise changes, those with hypertension need easily adopted, effective and manageable exercise interventions as a first line option. Meta-analyses indicate that isometric exercise (IE) results in larger reductions in BP compared to more traditional forms of exercise
^15^ and has great potential to treat hypertension,
^19^ improve health and reduce mortality. Isometric exercise can lower BP in people with both normal
^20^ and high-normal BP (pre-hypertensive)
^21^ and is a potentially effective lifestyle intervention for hypertension. IE involves holding a fixed position for a period of time: muscles are used but there is no movement, e.g. leaning against a wall in a seated position (
Figure 1). Only 24 minutes of IE a week are required to achieve reductions in BP of 12/6 mmHg in pre-hypertensives, which can be easily carried out at home without costly equipment.
^21^

**Figure 1. f1:**
[figure not shown]
Person performing the wall squat exercise.

Our feasibility study demonstrated that an IE wall-squat is deliverable, acceptable to patients and professionals, has low dropout and no adverse effects.
^22^ This article describes the protocol for the ISOFITTER study, a follow on randomised controlled clinical trial to determine the effectiveness and implementation potential of individually tailored IE training, at home for people with Stage 1 and 2 hypertension.

## Trial design and setting

This study is a multi-centre randomised, controlled trial (RCT) of an isometric exercise intervention for participants with Stage 1 and Stage 2 hypertension following an effectiveness-implementation hybrid type-1 design.
^23^ The RCT will involve parallel study groups of standard care plus IE (intervention group) versus standard care alone (control group).
Figure 2 presents a flowchart of the study design. The study will be delivered direct to public through advertising and primary care participant identification centres across England and Wales. Our geographical areas of focus are East Midlands, Yorkshire and Humber, South London, South-East England and Wales.

**Figure 2. f2:**
[figure not shown]
ISOFITTER Study Flowchart.

## Study objectives

The aim of the ISOFITTER study is to determine the effectiveness of self-prescribed IE at home in addition to standard care for reducing systolic BP in people with Stage 1 and 2 hypertension and understand contexts for implementation.

Primary objective: to determine the effectiveness of IE in reducing systolic BP in people with stage 1 and 2 hypertension compared to standard care.

Secondary objective: to understand relevant implementation contexts that support the ability to take up the intervention from a participant, provider/commissioner and cost perspective to explore:
•participant acceptability, adoption and feasibility, relevant to experiences in the ability to take up, self-administer/conduct the IE programme, and barriers and facilitators for long-term adherence;•healthcare provider and stakeholder perspectives (including commissioners) of sustainability and implementation into standard care pathways;•cost consequence analysis to provide a range of cost information to support commissioning decisions from outcomes.

## Protocol

The current version of the ISOFITTER protocol at the time of publication was Version 2, 15
^th^ January 2025.

### Participant eligibility criteria

Participants included in the study must be aged 18+ with stage 1 or stage 2 hypertension (defined as a clinic BP of ≥140/90–179/119 mmHg diagnosed by a health care professional and confirmed by a GP). Participants should be prescribed no more than 1 antihypertensive agent and have no significant medical condition that would contraindicate their participation. They must be able to undertake an IE intervention and able to self-monitor
BP.

A significant medical condition that would contraindicate participation outside of the exclusion criteria below is any medical condition declared by the participant or identified by the recommending physician which may affect a participant’s safety during the study (e.g. significant knee pain or weakness, epilepsy, narcolepsy etc).

Exclusion criteria include: alteration to antihypertensive medications within 6 weeks prior to screening (either dose or number of medications); receiving a β-blocker; averaged home systolic BP <120 mmHg following 3 days screening, ischaemic heart disease, stroke or transient ischaemic attack in the past 3-months; moderate or severe valvular heart disease, atrial or ventricular arrhythmia, congenital or inherited heart condition; pregnancy or actively trying to conceive; enrolled in Clinical Trial of Investigational Medicinal Products (CTIMP)/device/other interventional study of BP; locomotor abnormality resulting in inability to do wall squat or any condition that would be made worse by doing the wall squat exercise.

Exclusion of participants who were taking beta adrenergic blocking agents (beta-blockers) is due to attenuated heart rate, blood pressure and haemodynamic responses which would potentially undermine efficacy when prescribing this as well as other forms of exercise to lower resting blood pressure. Whilst this approach may exclude a proportion of people with hypertension treated, we think this would be relatively few. This is because our study only includes people on a single antihypertensive agent and beta-blockers are fourth-line agents in the treatment of uncomplicated hypertension according to NICE guidelines.
^1^

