### Participant recruitment

This study will utilise recruitment through up to 20 General Practice participant identification centres (PICs), using direct to public advertising through posters, public flyers, media including social media, associated partners and charities (e.g. Healthcare providers, Blood Pressure UK, British and Irish Hypertension society) and through outreach activities for under-represented groups. Demographics of participants recruited will be closely monitored across age, sex, disability, ethnicity and socioeconomic status to identify any under-represented groups against an expected representative sample calculated from UK hypertension prevalence data and UK population data. This will help guide targeting of under-represented groups and achieving a representative sample as discussed below. All participants will be directed to a pre-screening online form in the form of an advertisement or flyer with QR code or direct link. In GP recruitment PICs, a standardised search will identify potentially eligible participants from their medical records who will receive a text message with a link to the pre-screening form online. These searches and eligibility screening tasks will be done by the direct care team, or where appropriate by the National Institute for Health and Care Research (NIHR) regional RDN agile team. For outreach recruitment, participants may complete the pre-screening form in person with a member of the research team or wider partner organisations and events.

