### Participant consent

All participants in this study are required to provide informed consent prior to any interventions or assessments. Pre-screening eligibility form data is collected anonymously and permission to use unidentified data entered in the online form is confirmed in the pre-screening form prior to full informed consent. This allows important screening demographic information to be collected anonymously, including date of birth, gender, ethnicity, socioeconomic status, level of education and sexual orientation. These data will help to understand and monitor the diversity of participants interested in taking part in the study. Data for all those who complete the pre-screening form, regardless of whether they are eligible or not, will be retained to inform purposeful recruitment strategies to reach underserved groups, unless the participant does not agree to their data being used in this way. Where the participant is eligible at pre-screening and enters their contact details, their demographic information will be linked to their study ID number and future data automatically upon full study consent to avoid duplication of data collection at baseline.

Only participants with capacity will be included in the study. The study will be delivered remotely, and informed consent is completed by the participant online after receiving the online full information sheet and after online pre-screening to determine eligibility. Where needed the informed consent form can be emailed/posted as well as the option to go through consent with a member of the study team if they wish for accessibility. Support is available if participants require assistance to consent online or via paper consent. Informed consent is collected in the secure online research electronic data capture (see data management section). Where interested participants are identified in person or at outreach events, consent can be taken at these in person events with appropriate countersignature. Alternatively, they can complete informed consent at a later date either with the study team or recruitment site teams to consent using our alternative options (as above). Once a participant has consented to the study, they will be allocated a unique Participant Identification Number, a copy of the electronic consent form or the paper form (where used) will be provided to the participant (by email or post) and a copy held centrally in the Trial Master File.

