### Participant enrolment

**
*Pre-Screening and Participant Information*
**

An online pre-screening eligibility form with questions based on the study inclusion and exclusion criteria including: age, their blood pressure (confirmed by their GP), all medications, antihypertensive medication, medication changes within the last 6 weeks, if they experienced any of the excluding conditions in the past 3-months, pregnant and whether they are enrolled in another CTIMP/device/other interventional study of BP. If pre-screening eligibility is confirmed, participants are notified that they appear to be eligible for the study and are presented with a short summary of the study. They then have the option to enter their email address to receive the full study information. If identified as eligible, participants will be sent a maximum of two email reminders if they do not sign up directly after pre-screening.

The participant is then sent via email, text or post, a Participant Information Sheet (PIS) and link to the online consent form. The study website displays a downloadable PIS for participants and they will also be able to request the PIS by post or email if they prefer. For other recruitment routes where potentially eligible participants are recruited in person (e.g. outreach events), copies of the PIS will be available. The study website will also have details of a dedicated telephone, text and email address of the delivery team where interested participants can ask further questions or for the information to be read to them. At GP recruitment PICs, in-person support may also be available to discuss the study. Where translation into other languages may be needed, participants will be signposted to translate the information documents online (via Google). Those interested will be prompted to take sufficient time (ideally at least 24 hours) to consider the information prior to consenting to take part. Participants will also be encouraged to discuss taking part in the study with their GP if needed.

Further contact details (name, postal address, email confirmation, mobile number) as well as GP name and address are collected at the end of the consent process in order facilitate:

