•sending out automated blood pressure devices for participant screening and beyond;•sending out of study documents if requested or required for accessibility reasons;•sending of a GP letter to participant’s GP practice to inform them of study participation and what this involves;•setting up access to participant portal online with digital resources including instructional videos;•mobile and email reminders of study assessments and training if assigned to IE group.

**
*Screening*
**

After successfully completing pre-screening and upon receipt of their home blood pressure monitor, they will be instructed via email to measure their blood pressure for 3 days consecutively at home, taking 3 measurements in the morning and evening according to European Hypertension Society and NICE guidelines.
^1^
^,^
^26^ Measurements will be conducted using the home BP device (Kinetik Wellbeing WBP1 model number TMB-1775-A and model TMB-2287-K for those requiring an extra-large cuff
) provided by the study which will be mailed to the participant along with an instruction sheet and participant diary. Participants are instructed to continue normal activities during the screening period. Participants are made aware in the PIS and again prior to entering their screening data that a final decision about their eligibility to participate in the study after collection of:
•past medical history (in relation to eligibility criteria)•current medication•3 days of home blood pressure measurements•confirmation of ability to do IE

The calculation of blood pressure for entry into the study is conducted using the 2nd and 3rd reading on the 3 consecutive days morning and evening (total of 12 readings used to calculate the average home blood pressure). The average of all readings for home blood pressure is conducted to ensure we aren’t including people with either overtreated hypertension, white coat hypertension or people mis-diagnosed as hypertensive. Eligibility is then assessed against the full criteria. Those who screen fail will be sent an email thanking them for their contribution to the study and provided with website links for maintaining a healthy blood pressure and lifestyle (the same standard care advice provided to all participants in the study). Those who pass screening then proceed to randomisation and enrolment in the study as below.

**
*Randomisation*
**

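### The home BP average calculated for entry has a floor but no stated ceiling; only the clinic reading is capped at 179/119 (minor, rare, nearly free to fix)

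*Protocol article*

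**What the plan says.** Four statements in the Protocol article bear on this.

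- **Clinic limits.** Under Participant eligibility criteria, stage 1 or 2 hypertension is "defined as a clinic BP of ≥140/90–179/119 mmHg diagnosed by a health care professional and confirmed by a GP". The value reaches the trial through the form described under Participant recruitment: "All participants will be directed to a pre-screening online form".
- **Home limit.** The same eligibility section excludes people with "averaged home systolic BP <120 mmHg following 3 days screening". It gives no upper home value and no diastolic home value.
- **Home average.** Participant enrolment (Screening) describes the BP calculated for entry, with a "total of 12 readings used to calculate the average home blood pressure". The reasons given for it all concern people whose BP is too low: overtreatment, white coat effect and wrong diagnosis. Eligibility is then checked against all the criteria, and those who pass are randomised.
- **High readings.** Participant on study timeline and assessments says that participants above 180/120 will be advised to seek urgent review. That section opens by limiting itself to what happens after randomisation.

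Two exclusions under Participant eligibility criteria could be used at discretion. One covers a medical condition, declared by the participant or identified by the recommending physician, "which may affect a participant’s safety during the study". The other covers conditions that the wall squat would aggravate. Neither gives a BP value.

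**The concern.** The ceiling sits on one measurement and the floor on another. The clinic reading comes from outside the trial. The home average is the trial's own measurement, taken just before randomisation, and it is limited at the low end only.

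As an illustration, take a person with a clinic BP of 175/105 and a home average of 182/108. The clinic value is inside the stated range and the home value is above the floor, so no BP criterion stops entry. The same person's systolic average lies above the 180 figure that the trial uses for urgent review.

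The stake is participant safety, on a small scale. The intervention is unsupervised exercise at home ("The study will be delivered remotely"). Adverse event monitoring names BP spikes as a possible effect if the breath is held, with breathing instructions as mitigation, so the expected harm is low.

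**Working it through.** **Step 1. Which rule acts on which reading**

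| Reading | Lower limit | Upper limit | Effect |
|---|---|---|---|
| Clinic BP, GP-confirmed | 140/90 | 179/119 | entry criterion |
| Home average, 12 readings | 120 systolic | none stated | entry criterion |
| BP during the study | none | 180/120 | advice to seek review |

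The second eligibility check cannot supply a home ceiling, because the stated criteria hold none for it to apply.

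**Step 2. The denominator**

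The plan gives no figure for how many people this concerns. The count below uses its 542 randomised, which reproduces:

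- Normal approximation: n per arm = 2 × (1.960 + 1.282)² × 14.4² / 5² = 174.3, so 175.
- t-test version: 175.3, so 176 per arm and 352 in total.
- Attrition: 352 / 0.65 = 541.5, so 542.

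**Step 3. How many people**

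The article gives no baseline home BP distribution, so these inputs are assumptions:

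- Home systolic H is normal with mean m = 135, 140 or 145 and SD s = 12 or 15.
- Clinic systolic C has mean m + 5 and the same SD. The 5 mmHg is the gap between the two systolic thresholds in the Introduction ("defined as a clinic BP of ≥140/90 mmHg or a home BP measurement ≥135/85 mmHg").
- The correlation r between H and C is 0.5, 0.6, 0.7 or 0.8.
- Entry requires H ≥ 120 and 140 ≤ C ≤ 179.

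Given H = h, C has mean m + 5 + r(h − m) and SD s√(1 − r²). The expected count is

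542 × P(H ≥ 180 and 140 ≤ C ≤ 179) / P(H ≥ 120 and 140 ≤ C ≤ 179),

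by numerical integration over h:

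| m, s | r = 0.5 | 0.6 | 0.7 | 0.8 |
|---|---|---|---|---|
| 135, 12 | 0.09 | 0.08 | 0.07 | 0.05 |
| 135, 15 | 1.31 | 1.19 | 1.001 | 0.73 |
| 140, 12 | 0.32 | 0.28 | 0.24 | 0.17 |
| 140, 15 | 2.77 | 2.48 | 2.05 | 1.47 |
| 145, 12 | 1.004 | 0.89 | 0.72 | 0.50 |
| 145, 15 | 5.59 | 4.91 | 4.00 | 2.82 |

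- Highest: 542 × 0.00727 / 0.7048 = 5.59.
- Lowest: 542 × 0.0000478 / 0.4975 = 0.052.
- The count is below 1 in 12 of the 24 scenarios.
- The exercise arm carries half: 0.05 / 2 ≈ 0.03 to 5.6 / 2 = 2.8 of 271.
- A simulation of 20 million draws at m = 145, s = 15 gave 5.56 (r = 0.5) and 2.79 (r = 0.8).

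**Step 4. Sensitivity**

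Someone could qualify on diastolic BP with a clinic systolic below 140. Removing the clinic floor altogether gives 0.03 to 4.3 of 542. A higher assumed home mean raises the count: with mean 150 and SD 15, and no clinic limits, 542 × 0.02275 = 12.3.

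**The case against.** The strongest objection is that this is an absence in a condensed article. The exclusion list is introduced as a list of what is included, and the full protocol (Version 2) is said to be in the study repository. A home ceiling may stand there. That possibility remains and limits the remedy. It does not remove the point, because the article prints a numeric entry rule for the home average and fixes one side of it only.

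The second objection is that the split is deliberate: the clinic reading caps severity and the home average removes people who are not truly hypertensive. This explains the floor. It gives no reason for leaving high home averages unused when they are already in hand.

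The third is that high readings are acted on. Table 1 has home readings in its Screening column and every BP the study takes is a home reading, so the urgent-review advice can fairly be read to reach screening. It is still advice to seek care and does not hold up randomisation.

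Two stronger readings are tempting. A reader might infer that such a person is bound to be randomised, or that only one clause could stop it. The documents do not support that, since both the general safety clause and the exclusion for conditions aggravated by the wall squat leave room for judgement. A reader might also infer from the Introduction's 5 mmHg gap that the home ceiling should lie below 180/120. That gap is stated at the diagnostic threshold only, and nothing in the article carries it up to the severe range.

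**Conclusion.** The point holds as a minor one. The stated rules cap the clinic BP and not the home average, so they could admit a person whom the trial would also send for urgent review. Exclusion would then depend on discretion and not on a stated BP value.

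It is rare under the assumptions made: about 0.05 to 5.6 of 542. The documents cannot confirm that range, because the mean, SD, clinic-home gap and correlation are all assumed. The count covers systolic BP only.

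A reader might infer a threat to the trial's result. There is none: sample size, power and the primary analysis do not depend on a handful of such people.

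**What to change.** Add to the exclusions under Participant eligibility criteria: averaged home screening BP ≥180 mmHg systolic or ≥120 mmHg diastolic. This continues directly from the 179/119 clinic ceiling and uses the trial's own urgent-review figures. Under Participant on study timeline and assessments, state that the urgent-review advice also applies to home readings taken at screening.

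If the full protocol already holds this ceiling, only the article's wording needs the addition.

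The cost is one eligibility line, one clause and an automatic check on readings already entered before randomisation. The downside is a handful of extra screen failures at most.
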